### Outcomes

The primary outcome is defined as the successful weaning from IMV of high-risk patients before discharge from the ICU or from the weaning centre.

Secondary outcomes are:Time from intubation to successful weaning during hospitalisation in hours on the ventilator.Successful weaning for at least 48 consecutive hours in the intervention group, regardless of patient ventilatory status at discharge.Mortality during the in-patient stay.Re-hospitalisation for the same indication within 30 days of discharge.Use of emergency services within 30 days and within 3 months of discharge.No need for IMV 3 months after discharge.Utilisation of rehabilitation services within 3 months of discharge.Re-hospitalisation with IMV within 6 months of discharge.Mortality at 6 and 12 months.

Patients who either die before successful weaning, require continued IMV at hospital discharge, or cannot be discharged within 6 months of starting IMV or by 30th June, 2023, are considered weaning failures. June 30th, 2023, is the last date for which comparison data are available and thus represents a pragmatic threshold to ensure comparability of the intervention and comparison groups.

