### Sample size

For the purpose of power estimation, we assumed that 1,495 high-risk patients per group would be recruited. Further, we assumed patients are recruited in 40 cooperating ICU with an average cluster size of 25 and an intra-class correlation coefficient of 0.1, yielding a design effect coefficient of 3.4 [32]. Incorporating this into our power calculation would give us an effective sample size of 439 in both groups. Presuming a drop-out rate of 10.6%, we would reach an effective sample size of 393 in both groups. Assuming a rate of 20% weaning failures in the intervention and 30% in the comparison group, a chi-squared test with a significance level of 5% would have a power of 90% to detect a difference between the treatment and the comparison group. The actual primary analysis will be based on a mixed logistic regression model adjusted for various confounders including correlations within clusters, which can be expected to have better operating characteristics than a chi-squared test. This power analysis was conducted using PASS version 16.0.3.

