#### Final analysis

The primary outcome, successful weaning before discharge, will be evaluated using a mixed logistic regression model including treatment group, age, gender, acute COVID-19 pneumonia, pre-existing medical conditions via the Charlson Comorbidity Index (continuously) [33], number of ventilation cases of the centre, dependency on ventilatory assistance for at least 3 month within 1 year before admission (with tracheostomy vs without tracheostomy vs none), tracheostomy within 96 h of intubation, extracorporeal support (yes/no), and centre as a random intercept. The analysis population for the primary endpoint will be restricted in order that a possible bias due to the selection effect of the screening window will be minimized. If necessary, missing values will be imputed via a multiple imputation approach. For patients included into the analysis population, intercurrent events (such as death) which would prevent patients’ successful weaning will be counted as weaning failures. A number of sensitivity analysis will be conducted to investigate the impact of the imputation strategy, the 7-day inclusion window, and the choice of covariates.

The analysis of secondary outcomes will include the calculation of appropriate summary measures of the respective empirical distributions (mean, standard deviation, median, interquartile range, minimum and maximum for continuous variables, and absolute and relative frequencies for categorical variables), as well as descriptive *p*-values. In addition, similar mixed models as described for the primary outcome will be used, logistic models for categorical outcomes and linear models for continuous outcomes. Time to event endpoints will be analysed using methods from survival analysis, including Kaplan–Meier estimates, log-rank tests and shared frailty models similar to the primary analysis model. As appropriate, graphical methods will be used to visualise the results. Missing data in secondary outcomes will not be imputed.

In an explorative analysis, clinical data collected within the trial will be used in to identify potentially relevant factors which could help to supplement the developed prognosis model. To this end, an elastic-net approach, as well as decision-tree based models will be used.

A detailed statistical analysis plan will be set up prior to the final analysis. R version 4.0.2 or higher (www.R-project.org) will be used to carry out the analyses.

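### Time to weaning is assigned to Kaplan-Meier and log-rank with no competing-risk method: if deaths and discharges on IMV are censored, 6-month weaning is overstated, and late entry is not handled

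*Protocol article*

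**What the plan says.** The Outcomes section of the protocol article lists, among the secondary outcomes, "Time from intubation to successful weaning during hospitalisation in hours on the ventilator". It is the one outcome clearly worded as a time.

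The same section then defines failure: "Patients who either die before successful weaning, require continued IMV at hospital discharge, or cannot be discharged within 6 months of starting IMV", or by 30 June 2023, count as weaning failures. In-hospital mortality ("Mortality during the in-patient stay") and mortality at 6 and 12 months are separate secondary outcomes.

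Under Final analysis, the paragraph on the primary outcome says that "intercurrent events (such as death) which would prevent patients’ successful weaning will be counted as weaning failures". The next paragraph, on secondary outcomes, makes the p-values descriptive and gives the method for times: "Time to event endpoints will be analysed using methods from survival analysis, including Kaplan–Meier estimates, log-rank tests and shared frailty models". It adds "Missing data in secondary outcomes will not be imputed". It does not say whether a patient who dies ventilated, or leaves on IMV, is censored or kept as a failure in the time analysis. A detailed analysis plan is to follow.

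On entry, patients in participating units are screened while on IMV between 96 hours and 11 days. Comparison patients need at least 96 hours of ventilation and, for the primary assessment, must not die within 11 days of starting ventilation. The restriction meant to limit bias from the screening window is stated for the primary endpoint.

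**The concern.** A patient who dies on the ventilator can no longer be weaned, and one discharged on IMV can no longer be weaned during that hospital stay. Kaplan-Meier with these patients censored treats them as if they would go on to be weaned at the same rate as those still ventilated. Its complement then estimates weaning in a setting where nobody dies or leaves ventilated, not the proportion actually weaned. A log-rank test or frailty model on the same data compares the rate of weaning among those still at risk. It says nothing about how many left the risk set by failing.

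The second issue is entry. An intervention patient enrolled on day 8 cannot have been weaned between hour 96 and day 8. A comparison patient can have been, because only 96 hours of ventilation are required. With the clock at intubation and no delayed entry, that stretch counts as event-free time in the intervention group only. Other things equal, this makes the intervention look slower.

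At stake are the weaning curves and any statement that one group was weaned sooner or more often over 6 months.

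**Working it through.** **The plan's own figure.** None is given for time to weaning. The expected failure rates come from the power statement: "Assuming a rate of 20% weaning failures in the intervention and 30% in the comparison group". That statement reproduces: design effect 1 + 24 × 0.1 = 3.4; 1,495 / 3.4 = 439.7; × (1 − 0.106) = 393 per group; two-sided 5% chi-squared power for 20% vs 30% = 0.901, against the stated 90%. So 80% and 70% weaned are taken as the 6-month targets.

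**Assumptions not in the documents.** Constant hazards over 180 days, *a* for weaning and *b* for death or discharge on IMV; 1% to 5% of patients still ventilated at day 180 (part of the failures); the first 96 hours ignored in steps 1 to 3.

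**1. Formulas.**
- True weaning by day *t*: *a*/(*a*+*b*) × [1 − exp(−(*a*+*b*)*t*)].
- Complement of Kaplan-Meier with failures censored: 1 − exp(−*at*).
- With fraction *r* still ventilated at day 180, *a*+*b* = −ln(*r*)/180, split in proportion to weaned and failed.

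Example: 80% weaned, *r* = 1%. *a*+*b* = 4.605/180 = 0.0256; *a* = 0.0256 × 0.80/0.99 = 0.0207; 1 − exp(−0.0207 × 180) = 0.976, against a true 0.80.

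**2. Results.**

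| True at day 180 | Still ventilated | 1−KM, day 180 | True, day 28 | 1−KM, day 28 |
|---|---|---|---|---|
| 80% | 1% | 97.6% | 41.3% | 43.9% |
| 80% | 2% | 95.9% | 37.2% | 39.2% |
| 80% | 5% | 92.0% | 31.4% | 32.5% |
| 70% | 1% | 96.1% | 36.2% | 39.7% |
| 70% | 2% | 93.9% | 32.6% | 35.3% |
| 70% | 5% | 89.0% | 27.4% | 29.1% |

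The excess is 12 to 18 points (true 80%) or 19 to 26 points (true 70%) at day 180, and 1.1 to 3.5 points at day 28.

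**3. What the log-rank test sees.** Simulation: 2,000 runs, 393 per arm, no clustering.
- Equal weaning hazard of 0.03 per day (assumed), failures 20% vs 30%, so *b* = 0.03 × 0.2/0.8 = 0.0075 and 0.03 × 0.3/0.7 = 0.0129. True 6-month weaning is 80% vs 70%, but 1−KM is 99.5% in both arms. With failures censored the test rejects in 5.2% of runs; with failures kept at risk to the limit, in 67%. At this faster pace the day-28 excess is larger: 56.8% against a true 52.0% and 48.9%.
- A constructed case: one arm with 1.2 times the weaning hazard but 30% vs 20% failures. The censored test favours that arm (mean Z +2.2); with failures kept at risk it goes against it (mean Z −1.6).

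If failures stay in the risk set to the limit, 1−KM equals the cumulative incidence and the excess is zero.

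**4. Late entry.** The gap between hour 96 and enrolment is 0 to 7 days. The share of ventilated patients weaned in a gap of *g* days is about 1 − exp(−*ag*). For *a* from 0.0123 (lowest in step 2) to 0.03, a 4-day gap gives 1 − exp(−0.049) = 5% to 1 − exp(−0.12) = 11%; a 7-day gap gives 1 − exp(−0.086) = 8% to 1 − exp(−0.21) = 19%. These weanings can occur in the comparison group but, for a patient enrolled at the end of that gap, not in the intervention group. Handling competing events correctly does not remove this.

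**The case against.** The strongest reply is that the article states no censoring rule. Its list of methods is open, and censoring conventions commonly go to the analysis plan. The failure definition in Outcomes follows the whole outcome list; carried into the time analysis, with failures kept at risk to the limit, it removes the competing-event bias. This stands: a reader might infer that the curves will certainly be wrong, and the documents do not support that. What remains is that the named estimator, in its standard use, does not give a weaning probability here, and nothing in the article prevents that use.

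A reader might also infer a contradiction with the primary analysis, which counts death as failure. There is none. A cause-specific comparison of weaning hazards is valid and answers a different question; the error would be to read it, or 1−KM, as overall benefit.

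Nor would excess deaths go unnoticed in the trial: the primary outcome counts them and mortality is reported separately. The status of needing no IMV 3 months after discharge is categorical, falls under the logistic models, and is untouched by this point.

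On late entry, both groups share the first 96 hours, so only the following interval of up to 7 days can differ. Sensitivity analyses of the 7-day window are planned, but they are described with the primary outcome, as is the restriction of the population. The point therefore stands for time to weaning.

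**Conclusion.** The point holds conditionally. The plan names Kaplan-Meier, log-rank and shared frailty for an outcome that 20% to 30% of patients are expected never to reach, and names nothing for the events that prevent it. If those failures are censored, 6-month weaning is overstated by about 12 to 26 points and the log-rank test is blind to a pure difference in failures. The early part of the curve is little affected in the scenarios tied to the plan's own rates. These sizes rest on constant hazards, an assumed 1% to 5% still ventilated at day 180 and, for the tests, an assumed weaning hazard of 0.03 per day without clustering.

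The entry problem is independent of the censoring rule. Its direction is against the intervention, and its size depends on the unknown distribution of enrolment times.

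The outcome is secondary with descriptive p-values, so no confirmatory conclusion depends on it. The change is still worth making before the analysis plan is fixed.

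**What to change.** For time to weaning, specify in the analysis plan:

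- Aalen-Johansen cumulative incidence, with death and discharge on IMV as competing events. Equivalently, keep failures in the risk set to the 6-month limit, or to 30 June 2023 for patients whose 6 months would run past that date.
- Log-rank and shared frailty results labelled as cause-specific and shown beside the same model for death, or a Fine-Gray model in addition.
- Delayed entry at enrolment in the intervention group and at a comparable ventilation time in the comparison group; or apply the primary endpoint's screening-window restriction to this outcome as well.
- Kaplan-Meier retained for all-cause mortality.

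The cost is a few sentences in the analysis plan and standard R code, with a little more analysis work on a descriptive outcome. No new data are needed.

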### Data protection

Data protection is guaranteed in accordance with the European Data Protection Regulation, the Baden-Württemberg State Data Protection Act, and the Federal Data Protection Act. Furthermore, the data protection concept has been reviewed and accepted by the data protection officer of the Heidelberg University Hospital.

## Discussion

### Strenghts

The study will draw attention to weaning and all of its facetsThe study allows to share expertise and improve patient care in clinics without weaning expertiseThe study will improve the collaboration between the intervention team, consisting of specialised weaning physicians and respiratory therapists, the weaning centres and intensive care personal and thus strengthen the role of specialised personal

### Limitations

Intervention procedures may be applied heterogeneously in this field studyThe study is not blinded and not randomised

## Data Availability

Results are planned to be published in open access journals and reports will be available at the funding institution. The datasets used and analysed during the current study are available from the corresponding author on reasonable request.

## Abbreviations

AOK-BW: Allgemeine Ortskrankenkasse Baden-Württemberg
eCRF: Electronic case report form
ICU: Intensive care unit
IMV: Invasive mechanical ventilation
PRiVENT: Prevention of invasive ventilation
